## Abstract

Suffering from a chronic disease (CD) in adolescence can significantly impact the emotional health of adolescents and their families. MHealth can be a useful tool for these groups. However, few intervention programmes include the family system. The aim is to design an intervention programme (10Vida) for a paediatric population with a CD, and their families, to improve their adaptation to the disease. The study is a quasi-experimental repeated measures design in a open study, where the patients themselves, and their families, are their own control group. Participants will receive an intervention of seven individual sessions: five sessions with each patient, and two sessions with their caregivers. In the case of the patients, the aim is to improve their emotional state, their self-esteem, and their emotional competencies, reducing their perceived threat of illness. Furthermore, in the case of the caregivers, the aim is to improve their emotional state and reduce their burden. Indirectly, working with caregivers and those being cared for will improve family ties. The pilot study will involve 25 to 30 chronically ill adolescents aged between 12 and 16 years and their primary caregivers. Following the results, the necessary modifications will be included, and the programme will be offered to adolescents and their families who are willing to participate.

## 1. Introduction

Adolescence is a period characterised by a multitude of changes at the biopsychosocial level, all of which also implies many challenges [1]. If the diagnosis or the presence of a chronic disease or condition (CD) is added, the adjustment of the adolescent to this period becomes even more difficult [2]. The World Health Organisation [3] defines chronic diseases (CDs) as “long-lasting and usually slow-progressing diseases’’. Among the main child juvenile CDs are the allergic, the endocrine (in particular, type 1 diabetes mellitus (T1DM) and short stature (SS)) and the respiratory, such as bronchial asthma (BA) [4,5]. A chronic disease is characterised by unforeseeable changes in the course of the disease, a reduction in physical capacity, changes in appearance, a prolonged dependence on medical specialists, continuous treatments, and the need for assistance [6,7,8].

The presence of a CD in adolescence is a possible risk factor for developing a psychological disorder and for decreasing physical and psychological well-being [9].The most common psychopathology in a childhood juvenile CD is emotional, particularly anxiety symptoms, followed by depression symptoms, possibly leading to the development of an anxiety disorder or a major depressive disorder, although behavioural problems are also common [10,11]. However, the adolescent’s perception of their illness may mediate this relationship. Thus, adolescents with a higher perceived threat of illness tend to show poorer physical and emotional health outcomes [12,13,14].

The disease affects not only adolescents, but also their entire family system. When someone is diagnosed with a CD, the family as a whole is affected by the stressors associated with the disease and the side effects of treatment. There is an inevitable alteration to the whole family system, especially in cases where the patient is an infant or adolescent [7,15]. It is necessary to underline that studies indicate that most of the care of adolescent patients generally is undertaken by one specific member of the family, usually called the main caregiver [16]. Therefore, continued exposure to medical care, accompanying adolescents during medical visits, missing days of work, or even changing roles within the family can lead to overburdening or emotional problems for the main caregiver, such as anxiety or depression [17,18,19].

The stress due to the care tasks has been associated with anxiety and depression symptoms, often causing emotional disturbances in the caregivers, associating the above with greater emotional symptomatology in adolescents and a worse control of their disease [6,20]. However, as indicated above, the family is the main source of support when dealing with the disease. Therefore, factors such as family dynamics or attachment may favour the psychological adjustment of adolescents and their families [7]. Thus, social and family variables are fundamental in explaining emotional adjustment in adolescence [21]. Similarly, the enhancement of psychological strengths and virtues can be helpful in buffering the effects of stress [22,23]. Therefore, personal strengths are traits that are shown in the person over time that can help us to achieve well-being, which can be trained [24]. In this sense, programs aimed at their potentiation have focused especially on increasing social skills, openness to experiences, creativity, kindness, love, self-regulation, gratitude, and humour [25]. These programmes may be useful in addressing physical and emotional health in adolescents with CDs.

According to the American Academy of Paediatrics, medical treatment is insufficient for chronic paediatric diseases. There is a need to improve the child’s well-being or health-related quality of life, empowerment, and transition to healthy and productive adulthood. Many interventions in chronic diseases have been implemented in the scientific literature and have proven beneficial [26,27,28,29,30,31]. Generally, interventions have been based solely on the patient or the caregiver, with few interventions working together with both parties, as in the present study.

Typically, the types of interventions in this population have been characterised by educational techniques focused mainly on explaining the disease (psychoeducation) [32,33,34,35,36] and improving adherence. Clinical guidelines suggest a cognitive–behavioural approach to the psychological management of chronic diseases. It is essential to work with patients on coping strategies to help them deal with their symptoms, as well as disease care to improve their adherence to medical treatment and a better adaptation to the disease [37,38,39]. However, recent studies have shown how other psychological interventions, such as mindfulness [40,41], can improve the quality of life of adolescents with a chronic disease. Both at the individual and group levels, such interventions help manage the stress that negatively affects self-care behaviours and disease processes.

On the other hand, according to Iglesias [42], positive psychology has useful tools for controlling the disease, focusing on the individual’s psychological work for the emotional and physical stability of the patient. The most effective way to support them is through a safe and secure environment in the face of the disease. Interventions for CDs should be aimed at increasing self-confidence and self-efficacy, improving an optimistic explanatory style, and developing active coping strategies [43,44]

Finally, health interventions are currently being implemented through digital and technological platforms in patients with chronic diseases. The emergence of new technologies has provided a variety of tools that can be used, especially in the current COVID-19 pandemic situation [45,46]. MHealth is defined as “the practice of medicine and public health supported by mobile devices such as telephones, patient monitoring devices, digital assistants and other wireless devices” [47]. MHealth is a particularly useful tool for medical and psychological interventions in adolescents with CDs [48,49,50,51,52], especially as many need to minimise their contacts with other people [53]. Therefore, mHealth can be an opportunity to improve social relationships in this group, as well as increasing their social support, while working on improving physical and emotional health [10,48,49,50,51,52].

There are many programmes on psychoeducation with aspects related to the understanding of the disease, the symptomatology, the treatment, and the consequences of non-adherence. However, specific programmes on the emotional aspects of the acceptance of the disease in everyday life, as well as learning coping strategies, are needed for patients as a learning opportunity for the improvement of psychological well-being [26,27]. Psychological interventions in this area have primarily focused on the following components: disease beliefs, self-image and self-esteem, coping strategies and emotional competencies, and social support [37,44,54,55,56]. Of all the variables that have been focused on the different programmes, among the most important is the subjective perceptions or beliefs of the patient and their family regarding their illness [37,54,55], which can be an obstacle to treatment adherence. Another variable that has been of primary focus is self-esteem, which has been observed to be lower in adolescents with CD [44,56]. Considering the protective factors that a positive self-concept has on adjustment to stressful situations, different studies address the need to incorporate this variable as an outcome measure in intervention programmes [57]. In addition, as mentioned above, chronic illness at this stage can have a negative impact on the emotional well-being of adolescents. Therefore, working on emotional competencies, as previous studies indicate [26], is beneficial in reducing the emotional impact of the illness and fostering motivation to participate in self-care tasks. Finally, social relationships can be a protective factor, facilitating the adjustment to the disease [56]. It is necessary to assess their psychological adjustment and provide them with tools and support to participate in social activities without being prejudiced by their disease.

For interventions with families, the main focus has been to reduce the caregiving overburden [18,20,58] and allow for emotional ventilation, which contributes positively to a better adaptation to the disease by the patient [7,19].

To date, there are few intervention programs focused on adolescents with a CD and their families, and even fewer if they are approached through mHealth, an essential tool, given the global situation, that is on an individual basis to meet individual needs. That is why this research aims to (1) design an intervention program aimed at enhancing the strengths of adolescents with a CD and their families; and (2) analyse the effectiveness of this program on the indicators of the medical control of the different CDs (glycemic control, densitometry, analytical controls, spirometry, plethysmography, and the prick test) and well-being immediately after completing the training. The hypothesiss of the study is that adolescents will show a maintenance or improvement in physical and emotional health indicators after the implementation of the program.

## 2. Materials and Methods

Following the standard protocol items: recommendations for interventional trials statement, the current study protocol describes the details of the study rationale, proposed methods, organisation, and ethical considerations.

### 2.1. Study Setting

This study will be conducted in the different leading hospitals of the Valencian Community, in the Pneumology, Endocrinology, and Allergology units. This study is a quasi-experimental design with repeated measures. Each participant receiving the intervention (experimental condition)will also act as their control grorup. Therefore, the physical and psychological diagnostic measures will be collected from all of participants in an initial assessment (T1) and, secondly, six months after the initial assessment and right before starting the treatment programme (T2). At these two assessment points (T1 and T2), all participants (patients and family members) will be assessed (T2). The treatment lasted for five sessions for adolescents, with one individual session per month and two sessions for family caregivers (month 4 and month 5). The treatment programme will begin in the maximum expected time of 15 days from the second pre-treatment assessment (T2), with an estimated duration of 5 months. After the end of the treatment sessions for the patient and their family members, a new diagnostic test (T3) will be conducted (across all variables), within an expected maximum time of 15 days until the end of the treatment, to assess the post-treatment change. Thus, the estimated time between T1 and T2 is the same as that between T2 and T3, which is six months. The programme of registration, interventions, and evaluations (SPIRIT Programme) is shown in Table 1 and Table S1. 

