*Adaptation to chronic disease:* The Chronic Respiratory Disease Questionnaire (CRQ-SAS) [68] assesses aspects related to the adaptation to the disease (scale validated for the Spanish adolescent population by Valero et al. [69]). The psychometric properties are adequate (α = 0.85). The questionnaire on the adaptation to type 1 diabetes (RAE) [70] assesses aspects related to the adaptation to the disease, such as severity, adherence, psychological impact, discomfort, and health behaviours. Psychometric properties are adequate (α = 0.77). Finally, the Adolescent Rhinoconjunctivitis Quality of Life Questionnaire (AdolRQLQ) [71] is a quality of life assessment instrument specifically designed for the paediatric population with rhinoconjunctivitis. This questionnaire shows adequate psychometric properties (α = 0.77);*Parenting style of parents*: The Scale for the Evaluation of the Educational Style of Parents of Adolescents (EP) [72] allows for the assessment of the perception that adolescents have of their parents’ educational style;*Psychological well-being*: The Psychological Well-Being Scale for Adolescents (BIEPS-J) is a self-report measure developed [73] to determine the level of psychological well-being in adolescents (scale validated for the Spanish population [74]).

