### 2.5. Participants’ Timeline

The first pilot study started in February 2019, following the proposed structure with a small sample of six participants (adolescents and their families), and it was concluded in January 2020. Due to the pandemic, this protocol had to be adapted to a fully online format while maintaining the activities and variables studied. Currently, the February 2022 participants are being recruited for a second pilot study to test the intervention and improve the programme. The main study is scheduled to run from September 2022 to September 2024. Table 1 shows the timeline for the enrolment, interventions, and evaluations. The main objectives of phase I are the selection of the hospitals, the request for informed consent, and the baseline assessment. Firstly, the services of the hospitals that the research team has convened will be contacted. After meetings with the directors, informed consent will be requested from the families and adolescents participating in the programme. Before implementation, patients will be asked to complete a set of questionnaires. Phase II’s main objective is to evaluate the participating patients and family members, as they will constitute the control group. After six months, in phase III, the main objective will be implementing the intervention programme in the same sample as in phase II. After completing the intervention, in phase IV, participants will be re-evaluated. In the last phase, the effectiveness of the programme will be analysed.

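### With assessments about six months apart in a fixed untreated-then-treated order and no calendar term, an annual cycle can mimic or mask a programme effect unless enrolment is spread over the year

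*Protocol article*

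**What the plan says.** Labels here follow section 2.1 of the protocol article: T1 is the initial assessment, T2 the assessment just before treatment, and T3 the one after treatment.

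- **Spacing (2.1).** T2 falls six months after T1. Treatment starts at most 15 days after T2, "with an estimated duration of 5 months", and T3 follows "within an expected maximum time of 15 days until the end of the treatment". The section concludes: "Thus, the estimated time between T1 and T2 is the same as that between T2 and T3, which is six months".
- **Control (2.1, 2.5, 2.7).** The same families supply the untreated window first and the treated window second. There is no concurrent untreated group.
- **Model (2.8, Statistical Methods).** Change is regressed on the pre-intervention score and then on condition (1 = experimental, 0 = control). A significant condition term is attributed to the intervention. No term for calendar time appears.
- **Outcomes (2.4).** The secondary outcomes include spirometry, a respiratory questionnaire (CRQ-SAS) and the AdolRQLQ, which "is a quality of life assessment instrument specifically designed for the paediatric population with rhinoconjunctivitis". The primary outcomes are psychological scales. Objective 2 in the Introduction nevertheless names spirometry and other medical-control indicators.
- **Calendar (2.5).** The first pilot ran from February 2019 to January 2020 with six participants. On the second: "Currently, the February 2022 participants are being recruited for a second pilot study". On the main study: "The main study is scheduled to run from September 2022 to September 2024". Recruitment is at routine visits (2.7), with no enrolment month fixed.

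**The concern.** An own-control design removes change that would have happened anyway only if that change is similar in the two windows. A seasonal cycle is not: at six-month spacing, whatever it does between T1 and T2 it undoes between T2 and T3. Setting the treated window against the untreated one therefore adds the two seasonal movements together.

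For a cohort enrolled in one season, a seasonal outcome could seem to worsen while untreated and improve while treated, with no programme effect at all. Enrolled half a year later, the same cohort would show the reverse, and a real benefit could be hidden. The attribution rule in section 2.8 would credit either pattern to the programme. The comparison between disease groups that the Discussion looks forward to would also be affected if units recruited at different times of year.

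**Working it through.** **1. The plan's own interval.** From T2 to T3: at most 0.5 + 5 + 0.5 = 6.0 months, which reproduces the stated six months. Both 15-day terms are maxima, so the minimum is 0 + 5 + 0 = 5.0 months. T1 to T3 is therefore 11 to 12 months. Under an annual cosine cycle, the seasonal changes in the two windows have opposite signs for 100% of start dates at a 6-month gap (correlation -1.00) and for 92% at a 5-month gap (correlation -0.97).

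**2. Bias when all enrol at a seasonal extreme.** Let the seasonal level be S at T1 and T3 and S - D at T2, with no programme effect. I read section 2.8 as coding T1-T2 as 0 and T2-T3 as 1; the text does not say how one cohort yields two groups.

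- Simple T2-T3 change: S - (S - D) = D.
- Unadjusted difference of changes, (T3 - T2) - (T2 - T1): D - (-D) = 2D.
- Planned coefficient. The conditions differ by 2D in change and by -D in pre-score. With equal variances the slope of change on pre-score is r - 1. The coefficient is 2D - (r - 1)(-D) = (1 + r)D, or 1.5D at an assumed r = 0.5.
- T3 - T1: 0 at 12 months. At 11 months it is at most 0.52A, where A is the cosine amplitude and D = 2A, so about 0.26D.

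**3. Spreading enrolment.** With enrolment even over W months centred on the extreme, the mean bias shrinks by sin(πW/12)/(πW/12). The middle column takes r = 0.5 and ignores the small effect of the spread on the slope.

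| Enrolment window | Factor | Planned coefficient | Unadjusted difference |
|---|---|---|---|
| 1 month | 0.989 | 1.48D | 1.98D |
| 6 months | 0.637 | 0.95D | 1.27D |
| 9 months | 0.300 | 0.45D | 0.60D |
| 12 months | 0 | 0 | 0 |

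**4. In SD units.** D is an assumption. At a seasonal extreme with r = 0.5, D = 0.1, 0.2 and 0.4 SD bias the planned coefficient by 0.15, 0.30 and 0.60 SD.

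**5. Chance of declaring an effect when there is none.** Assumptions: two-sided 0.05, r = 0.5, normal approximation, unadjusted difference of changes with variance 6(1 - r)SD² plus seasonal spread. Entries are for enrolment windows of 1 / 6 / 12 months.

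| D | n = 30 | n = 200 |
|---|---|---|
| 0.2 SD | 24% / 13% / 5% | 90% / 55% / 5% |
| 0.4 SD | 71% / 36% / 5% | 100% / 98% / 5% |

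Pre-score adjustment barely changes these rates. It lowers the bias to 1.5D, but it also lowers the variance per participant to (1 - r)(r² + (1 + r)² + 1) = 0.5 × 3.5 = 1.75, against 3.0 unadjusted. At D = 0.2 the ratio of bias to SD is 0.30/1.32 = 0.227, against 0.40/1.73 = 0.231. The sizes are those of section 2.6 (25 to 30 per unit in the pilot, about 200 in the main study). Disease-specific scales apply to only part of the 200.

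**6. Room in the calendar.** The main study has 24 months and each family needs about 12, so at most about 12 remain for enrolment. In the first pilot, February 2019 to January 2020 spans at most 12 months and follow-up takes at least 11. Its six participants must have enrolled within about one month.

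**The case against.** The strongest reply is that nothing shows main-study enrolment to be bunched. Recruitment at routine visits, among patients diagnosed within the last six months, fits rolling entry. The 24-month schedule leaves room for a full year of it, and the average seasonal bias is then zero. This stands. A reader might infer from the September start that families enter as a September block, but section 2.5 gives only the dates of the study.

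A reader might also take 2D as the bias of the planned analysis. It is not: section 2.8 adjusts for the pre-score, which gives (1 + r)D, and 2D is only the limit as r approaches 1. Nor is T3 - T1 wholly free of season, since T3 can fall a month early.

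It is also fair to say that the documents give no seasonal amplitude for any outcome. The outcomes most plausibly affected are secondary, and section 2.4 allows them to be left out if numbers are low. The only cohort certain to have been bunched had six participants and is finished. To infer that the trial cannot answer objective 2 would go too far.

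Last, recruitment pacing and covariates are often left to a fuller document. Here, though, the article itself states the spacing, the model and the attribution rule, so the confounding follows from what is written. The Discussion's caveat that results may not be attributable to the programme is general: it neither names season nor removes it.

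**Conclusion.** The concern holds as a conditional one. Under the stated spacing and model, seasonal change is confounded with condition unless enrolment is spread over the year. It can create an apparent effect or conceal a true one, depending on when families enter. The bias in the planned coefficient ranges from 0 (even enrolment over 12 months) to (1 + r)D (all enrolled at a seasonal extreme), which is 1.5D at r = 0.5.

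This rests on assumed values of D and r, on a cosine-shaped cycle for the intermediate windows, and on T1-T2 being coded as control and T2-T3 as experimental. It matters mainly for AdolRQLQ, CRQ-SAS and spirometry, which are secondary but belong to objective 2, and for a pilot enrolled in one season. The second pilot was recruiting in February 2022, but the length of its recruitment is not stated. The documents do not support a claim that the main study will be biased, or that the primary psychological outcomes are seasonal.

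**What to change.** 1. **Model (2.8).** For AdolRQLQ, CRQ-SAS and spirometry, add calendar time of the pre and post assessments, as sine and cosine terms or as season. State that this separates season from study phase only when enrolment is staggered. In a cohort enrolled in a single month the calendar terms are collinear with condition.
2. **Sensitivity analysis.** Report the T3-versus-T1 change beside the main result as a season-matched check. Do not use it as a decision rule: it has no untreated comparator and includes a year of adaptation after diagnosis, so disagreement in direction would not by itself refute a benefit.
3. **Recruitment (2.7).** Where feasible, spread each unit's enrolment over the roughly 12 months that the main-study calendar allows. Where a cohort is enrolled in one season, do not attribute change in seasonal outcomes to the programme without stating this confounding.

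The first two items use assessment dates and scores already collected. They cost one or two model terms, a small loss of precision and one extra reported contrast. The third is the real cost: 24 months less about 12 of follow-up leaves little slack if recruitment is slow.
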